**Patients and Methods:** This open-label randomized clinical trial will be conducted at the Department of Otorhinolaryngology and Head Neck Surgery in collaboration with the Department of Virology and Department of Medicine in Dhaka Medical College Hospital (DMCH). The study will be conducted from September 2020 to December 2020. A total of 189 confirmed cases of COVID-19 disease proven by reverse transcription polymerase chain reaction (RT-PCR) testing will be enrolled in this study. Written informed consent will be ensured before participation. In case of no literacy, fingerprint will be considered for written permission. Consent will be sought from the legal guardian in case of minor or underaged. Formal ethical clearance will be obtained from the Ethical Review Committee (ERC) of Dhaka Medical College (DMC). All of the participants will be divided into seven Arms: Arm 1 will receive povidone iodine (PVP-I) nasal irrigation at a concentration of 0.4%, Arm 2 and Arm 3 will receive 0.5% and 0.6%, Arm 4 will receive PVP-I nasal spray at a concentration of 0.5% and Arm 5 will receive 0.6%. Arm 6 (placebo comparator group) will receive nasal irrigation with distilled water (DW), and Arm 7 (placebo comparator group) will receive nasal spray with distilled water. The contact time will be minimum 30 seconds. After the individual application of PVP-I and distilled water in the respective participants, they will be tested again for RT-PCR for COVID-19 from nasopharyngeal samples. All patients will be subjected to a detailed history, physical examination and adverse events. Computer generated randomization sequence will be followed for randomization. Data will be recorded in a semi structured questionnaire and will be analyzed by ‘R-4.0.2’ data analysis software.

**Conclusion:** It is expected that the study will reveal the virucidal activity with optimal contact time and concentration of nasal preparations of PVP-I against COVID-19. The results may help in prevention strategies for the general population, health care workers and COVID-19-positive patients.

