**Procedure of randomization:** The study participants will be randomly assigned in this study into seven (7) equal Arm, where each arm has equal opportunity to receive any treatment option. Randomization will be performed by computer generated random sequences.

- - Arm 1 will receive povidone iodine (PVP-I) nasal irrigation at a concentration of 0.4%
  - Arm 2 will receive povidone iodine (PVP-I) nasal irrigation at a concentration of 0.5%
  - Arm 3 will receive povidone iodine (PVP-I) nasal irrigation at a concentration of 0.6%
  - Arm 4 will receive PVP-I nasal spray at a concentration of 0.5% with standard care.
  - Arm 5 will receive PVP-I nasal spray at a concentration of 0.6%
  - Arm 6 (placebo comparator group) will receive nasal irrigation with distilled water
  - Arm 7 (placebo comparator group) will receive nasal spray with distilled water

This can be done quickly, with baseline information typically captured in <15 min. Recruitment & randomization will be performed contemporaneously with assessment/resuscitation of patients by a second person so that medical care is not delayed by recruitment. Patients will only be randomized once baseline data have been entered; after this has been done, participants will not be withdrawn from the study. Following tossing, the trial physicians reported the principal investigator (PI) of the trial, and then the PI handed over an opaque sealed envelope, which will be numbered sequentially to correspond to patient enrolment numbers, which will be used for concealment of treatment allocations. Envelopes will be kept in a locked drawer and will be opened in strict numerical order by supervisor in the presence of the nursing supervisor of the study unit. Allocation between arms will initially be equal, although this may be revised following guidance of the PI and his team (as per the statistical plan).

**Withdrawal of study participants:** Participants are free to withdraw from the study at any point, for any reason. If this occurs, the primary reason for withdrawal will be documented in the participant’s case record form. The participant will have the option of withdrawal from:

- Study medication with continued study procedures and collection of clinical and safety data,
- All aspects of the trial but continued use of data collected up to that point,
- All aspects of the trial with the removal of all previously collected data, or

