- All aspects of the trial with the removal of previously collected data and stored participant samples.

Randomized patients who wish to withdraw from the study before they have undertaken any study-related procedures will be replaced. Data on the original participant will be kept on the CRF/database if the participant agrees to this.

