**Dosing regimen:**

**Intervention Arms (Arms 1, 2, 3, 4, 5):** Participants allocated to PVP-I solution (especially prepared for the study) after confirmation of COVID-19 positivity. Proper dilution with normal saline will be added, which will be physically and chemically stable for 6 hours. Other supporting care (crystalloid solution infusion), and monitoring of vital statistics, in case of bleeding protective measures will be performed according to the national guidelines.

**Control Arms (Arms 6 and 7):** Participants allocated distilled water for nasal irrigation for Arm 6 a placebo that will also be reconstituted and applied at the same rate as mentioned in the invention groups and distilled water for nasal spray for Arm 7 a placebo that will also be reconstituted and applied at the same rate as mentioned in the invention groups.

In both Arms of patients, 10 ml of PVP-I or distilled water will be administered for 2 minutes. Nasal spray will be administered in each nostril using an atomizing device (2 sprays for average device). Control groups, will receive distilled water irrigation and distilled water nasal spray at similar amounts and durations. Further RT-PCR will be assessed within 1 minutes to 15 minutes of the following intervention.

**Participant compliance:** The study team will not create any problem with compliance while the patient is under care and supervision in the hospital. It will be ensured that all recruited patients will receive the appropriate interventions, although they could be interrupted due to the onset of potential adverse effects such as hypotension.

**Overdose:** The study team will titrate the drugs against the key adverse effect of hypotension. Nasal spray and nasal irrigation will be halted if patients complain of significant discomfort or clinically significant hypotension or signs of anaphylaxis. Procedures will be started again at a lower rate if the condition settles or according to the patient’s choice.

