**Responsibility sharing of care of the patients:** As the patients will remain under the care of the hospitals’ consultant physicians/unit head who will have primary responsibility for their management. Management protocols will be agreed upon between the medical team and study team. Decisions about intubation, requirement of blood and blood products, transfer of patients to intensive care, weaning of ventilation and extubation will be made by the medical team independently of study doctors. All decisions will be based on the patient’s clinical condition and the available hospital resources, as per usual hospital practice. The study team preferably by trial physicians will note down the record in the patient’s case record form (CRF).

**Prohibited Medications:** No medicines are specifically prohibited for this clinical trial.

**Non-investigational medicinal products:** All patients will receive standard care plus supporting care according to the “National Guidelines on Clinical Management of Coronavirus Disease 2019 (COVID-19)”. Among the standard care fluids, oxygen, ventilatory support, and antipyretics will be provided as necessary in all Arms of patients and will be decided by the chief/consultant of the admission unit. No other noninvestigational product will be used for the study purpose. In case of any product required for the best suited management, inclusion of this patient will be decided upon the opinion of the PI.

**Methods of data collection:** Data collection will be performed by the trial physicians. A paper based semi-structured questionnaire will be made and pretested before data collection. All potential participants will be recorded in this database at first contact and assigned a study number. This study number (e.g., DMC-PVP-I-0001) will be used for all data and samples collected from that person. Study doctors will recruit and randomize patients. They will not be able to predict allocation before randomization. Following randomization, allocation will be performed by the PI, and trial physicians or nurses will confirm the administration of either drug (0.4% or 0.5% or 0.6% PVP-I)/placebo (distilled water). Patients will be closely monitored. Temperature will be measured every 6 hours, and blood pressure, respiratory rate, and pulse rate will be measured every hour. Urine output will be measured in every 8 hours. Drug-related side effects or any adverse events will be observed in each group.

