If there is no reaction or unusual event, another RT-PCR sample will be collected from the nasopharynx and sent for further testing.

The total duration of the follow-up will be 2 days (or a person fulfills the discharge criteria). All clinical events will be noted in case record form by trial physicians, including vital status at hospital discharge. Data entry will be date/time stamped. Laboratory analysis data will be collected using the same CRF.

**Data quality and standards:** Following collection, all data sets and collected record forms will be checked. A formal clinical data management plan will be written before the study starts, agreed upon by the co-investigators and Data Monitoring Committee, and documented as a trial master file. Laboratory results will be discussed regularly between the PI and laboratory managers.

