**Proposed Analysis Plan of the study:**

Data analysis will be performed by data management software, R-4.0.2’. Then, the principal investigator (PI) will also check and verify the data. Then data will be transferred to statistician. If it is consistent with the objectives, then the PI and his team will draft the final result.

The following procedure will be followed during data analysis. The RCT aims to determine whether povidone iodine can clear COVID-19 virus from the nasopharynx of COVID-19 positive patients. The analysis will be performed on an intention-to-treat basis and a per-protocol basis. Subgroup analyses based on the primary outcome will also be estimated. Although the study is not formally powered for these subgroup analyses, the analysis will be added to draw a more conclusive statement. Statistical significance is set at the 95% confidence level at the 5% acceptable error level. Differences will be considered significant at the P < 0.05 level for all these tests. The data will be expressed as the means ± standard deviations (SD) for continuous variables and as frequencies (%) for categorical variables. Chi-square test and Student’s t test or ANOVA will be used in cases of normally distributed data, and similar non parametric data will be used whenever appropriate. Data will be analyzed by SPSS 20 Windows version (Chicago, Illinois, USA), and graphs and charts will be expressed by Microsoft Excel 2016.

.

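### One section makes the outcome swab conditional on no reaction while two others do not, which puts the intention-to-treat comparison at risk of informative missing outcomes

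*Protocol*

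**What the plan says.** The efficacy question is whether povidone iodine clears virus from the nasopharynx. The only measurement that can answer it is the nasopharyngeal RT-PCR taken after application. The protocol describes that test in three places:

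- Part-A, Patients and Methods: after application, "they will be tested again for RT-PCR for COVID-19 from nasopharyngeal samples". No condition is attached.
- Dosing regimen: "Further RT-PCR will be assessed within 1 minutes to 15 minutes of the following intervention". Again no condition.
- Methods of data collection: "If there is no reaction or unusual event, another RT-PCR sample will be collected from the nasopharynx and sent for further testing". Here the sample depends on nothing untoward having happened.

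The Proposed Analysis Plan states: "The analysis will be performed on an intention-to-treat basis and a per-protocol basis". Adverse events are a separate secondary objective. The Preparation of placebo paragraph confirms that nobody is blinded.

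Three further statements bear on who stays in the count. Withdrawal of study participants says: "Randomized patients who wish to withdraw from the study before they have undertaken any study-related procedures will be replaced". Data on the original participant are kept if he or she agrees. The same section offers, as one withdrawal option, "All aspects of the trial with the removal of all previously collected data, or". Non-investigational medicinal products says: "In case of any product required for the best suited management, inclusion of this patient will be decided upon the opinion of the PI".

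**The concern.** The conditional sentence makes collection of one outcome (clearance) depend on another (a reaction), and treatment can influence both. Five arms receive iodine at three concentrations and two receive water, so the share of patients left without a swab could differ by arm. What counts as a reaction or unusual event is not defined, and it is judged by staff who know the allocation. The Overdose paragraph itself foresees applications being halted for poor tolerance, so such events are expected.

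Two trial physicians could each follow this protocol faithfully and collect different data: one swabs everyone, the other skips patients who react. If the second reading is followed, some randomised patients have no outcome. A comparison of those swabbed is then no longer a comparison of the groups as randomised. With 27 per arm, each missing patient is 1/27 = 3.7% of the arm.

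**Working it through.** **Arm size.** The stated inputs are Z values 1.96 and 0.84, SD 10, difference 5 and ratio 1. They give 2 × (1.96 + 0.84)² × 10² / 5² = 62.72, so 63 per group and 126 in total, as stated. Then 63×2 + 30×2 = 186; 186/7 = 26.6, rounded up to 27; 27×7 = 189. The 27 per arm reproduces and is used below only as the denominator.

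**The passages side by side.** Two sections require the retest of all participants; one requires it only when no reaction has occurred. The protocol nowhere describes two separate post-application samples, so these are taken to be the same swab. The three statements cannot all be followed in a patient who reacts.

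**What the literal condition could do.** The protocol gives neither a reaction rate nor a clearance rate, so everything here is assumed. Let p be true clearance (the same in both arms, so no treatment effect), m the share of the active arm left unsampled, and c the clearance among those unsampled. The control arm is fully sampled.

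- Observed clearance in the active arm = (p − m·c)/(1 − m)
- Spurious difference from control = observed − p = m·(p − c)/(1 − m)

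Example: p = 0.50, m = 0.30, c = 0 gives 0.50/0.70 = 0.714, a false benefit of 21.4 points. With c = 0.75 it gives (0.50 − 0.225)/0.70 = 0.393, a false harm of 10.7 points.

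Spurious difference in percentage points:

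| Unsampled m (of 27) | p = 30%, c = 0 | p = 30%, c = 1.5p | p = 50%, c = 0 | p = 50%, c = 1.5p |
| --- | --- | --- | --- | --- |
| 5% (1.4) | +1.6 | -0.8 | +2.6 | -1.3 |
| 10% (2.7) | +3.3 | -1.7 | +5.6 | -2.8 |
| 20% (5.4) | +7.5 | -3.8 | +12.5 | -6.3 |
| 30% (8.1) | +12.9 | -6.4 | +21.4 | -10.7 |

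Whenever c = p the difference is 0.

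**Bounds without an assumption about c.** Each arm's clearance among all randomised is uncertain by its own missing share. The bounds on the difference are therefore as wide as the two missing shares added together: 5 points for 5% against 0%, and 35 points for 30% against 5% (active against control).

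**Counting every unsampled patient as not cleared is not neutral either.** If the unsampled clear at the same rate as the rest, with p = 50% and m = 30%, the active arm shows 0.70 × 0.50 = 35% against 50% in control, a false harm of 15 points. One imputation rule is therefore not enough.

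**The case against.** The strongest reply is that the condition is not a settled rule. Two other sections state the retest plainly, and the conditional sentence, which follows the text on monitoring for side effects, may be meant only as a safety pause before the swab. That is a fair reading. It makes the defect a contradiction to be resolved rather than proof that reacting patients go unsampled. The contradiction remains, because the sentence is worded as a condition and sits in the data-collection instructions.

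A second reply is that the handling of missing outcomes belongs in a statistical analysis plan, which is not at hand. That is right for imputation and the choice of primary set, and their absence is not criticised. It does not cover collection: a swab due 1 to 15 minutes after application and not taken cannot be recovered by any later plan.

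Several stronger conclusions are tempting but not supported:

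- **A reader might infer that the more irritating concentrations will look better than they are.** The direction is unknown; the bias can be positive, zero or negative.
- **A reader might infer that replacement and data removal add tolerability bias.** Replacement covers only patients who leave before any study procedure, so they cannot have reacted. Removal of data is the participant's choice and is not tied to a reaction. What stands is that, with open allocation, a refusal can follow knowledge of the arm.
- **A reader might infer that the principal investigator may rule out randomised patients.** The text speaks of inclusion, which may well mean enrolment, and does not say whether randomisation has already happened.
- **A reader might see a contradiction between "after this has been done, participants will not be withdrawn from the study" and the freedom to withdraw.** The first can mean that the study team will not remove anyone, which is compatible with the participant's own right and helps intention-to-treat.

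**Conclusion.** The point holds as a conflict between sections with a real consequence. If the conditional sentence is followed, the planned intention-to-treat comparison is exposed to outcomes missing for a reason that treatment can influence and unblinded staff judge. It does not follow that the comparison is necessarily biased or cannot be made: with no reactions, or with reactions unrelated to clearance, the bias is nil.

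The illustrated range, from -10.7 to +21.4 points, rests on 50% true clearance, no true effect, a fully sampled control arm, 5% to 30% of an active arm unsampled, and clearance among the unsampled of between none and 1.5 times the overall rate. None of these rates comes from the protocol. The conflict should be settled before enrolment, because a missed swab is lost for good. The replacement rule and the wording on inclusion are secondary.

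**What to change.** **Main change.** Reconcile the Part-A summary, Dosing regimen and Methods of data collection so that the outcome swab is due in every randomised participant on the same schedule and does not depend on a reaction as such. Exceptions for safety are for the clinical team to define and for the case record form to record. In the analysis, keep all randomised patients in the denominator by allocated arm, report the number unsampled and the reason by arm, and analyse missing swabs both as not cleared and as cleared.

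**Secondary changes.**

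- Count randomised patients who withdraw before any procedure as randomised. If a replacement is enrolled, give that person the next randomisation number and not the vacated slot.
- State that the principal investigator's decision on inclusion under Non-investigational medicinal products applies only before randomisation.

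**Cost.** These are mainly changes of wording. Some arms may end with slightly fewer than 27 evaluable patients, and the estimates may be slightly less favourable than an analysis of swabbed patients alone.

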**Proposed Analysis Plan of the study:**

Data analysis will be performed by data management software, R-4.0.2’. Then, the principal investigator (PI) will also check and verify the data. Then data will be transferred to statistician. If it is consistent with the objectives, then the PI and his team will draft the final result.

The following procedure will be followed during data analysis. The RCT aims to determine whether povidone iodine can clear COVID-19 virus from the nasopharynx of COVID-19 positive patients. The analysis will be performed on an intention-to-treat basis and a per-protocol basis. Subgroup analyses based on the primary outcome will also be estimated. Although the study is not formally powered for these subgroup analyses, the analysis will be added to draw a more conclusive statement. Statistical significance is set at the 95% confidence level at the 5% acceptable error level. Differences will be considered significant at the P < 0.05 level for all these tests. The data will be expressed as the means ± standard deviations (SD) for continuous variables and as frequencies (%) for categorical variables. Chi-square test and Student’s t test or ANOVA will be used in cases of normally distributed data, and similar non parametric data will be used whenever appropriate. Data will be analyzed by SPSS 20 Windows version (Chicago, Illinois, USA), and graphs and charts will be expressed by Microsoft Excel 2016.

.

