**Objectives:**

**General Objective:**

To determine the virucidal efficacy of povidone iodine on COVID-19 virus located in nasopharynx.

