**Investigational medicinal product and placebo:**

**Intervention for Arms 1, 2, 3, 4 and 5 (PVP-I group/treatment group):** Arm 1 will receive povidone iodine (PVP-I) nasal irrigation at a concentration of 0.4%, Arm 2 will receive povidone iodine (PVP-I) nasal irrigation at a concentration of 0.5%, Arm 3 will receive povidone iodine (PVP-I) nasal irrigation at a concentration of 0.6%, Arm 4 will receive PVP-I nasal spray at a concentration of 0.5% and Arm 5 will receive PVP-I nasal spray at a concentration of 0.6%. The contact time will be minimum 30 seconds.

**Intervention for Arms 6 and 7 (placebo comparator):** Arm 6 (Placebo comparator group) will receive nasal irrigation with distilled water, and Arm 7 (Placebo comparator group) will receive nasal spray with distilled water for the same duration as a placebo agent.

All groups of patients will receive standard medical care according to country guideline.

**Preparation of placebo:** As this study will be an open label study, no blinding will be performed and no dummy placebo will be made.

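### Drafting of the final result hangs on an undefined consistency check, made with allocation and results open, which leaves room for result-dependent reporting

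*Protocol*

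**What the plan says.** The opening of the Protocol's section on the proposed analysis plan sets out a sequence. The data are analysed in software. Next: "Then, the principal investigator (PI) will also check and verify the data". Next: "Then data will be transferred to statistician". It closes with: "If it is consistent with the objectives, then the PI and his team will draft the final result".

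Three other statements describe the position of the person who makes these checks:

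- Methods of data collection: "Following randomization, allocation will be performed by the PI".
- Data quality and standards: "Laboratory results will be discussed regularly between the PI and laboratory managers".
- Preparation of placebo: "As this study will be an open label study, no blinding will be performed and no dummy placebo will be made".

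The general objective is worded neutrally: "To determine the virucidal efficacy of povidone iodine on COVID-19 virus located in nasopharynx". The secondary objectives are to determine efficacy in clearing the virus and to assess adverse events. The analysis plan describes the aim as finding out whether povidone iodine can clear the virus. The conclusion in Part-A, by contrast, says in advance that virucidal activity is expected to be shown.

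**The concern.** A protocol should fix what will be reported before anyone has seen the results. Here the step from analysis to final result passes through a condition with no stated content, at a point where the results can be known. If such a condition can be met or not met according to what the data show, a reader of the eventual report cannot tell whether the analyses presented are all those planned or a selection.

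The people and the order of work add to this. The efficacy outcome is the RT-PCR result after the intervention. The PI is linked to allocation, to the laboratory discussions during the trial, and to the data check before the statistician receives the file, and the trial has no blinding. Open-label application of a spray or irrigation does not require the laboratory to know the arm, nor does it require arm to be open when results are discussed.

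**Working it through.** No arithmetic settles this point, and the Protocol gives no figure that bears on it. The check is a reading of the passages side by side.

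**1. Is it a stated rule or a gap?** It is a stated rule. The sentence has the form if–then, with drafting of the final result as its consequence. It is therefore not something that a separate statistical analysis plan would simply fill in.

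**2. What does the condition test?** There are three possible readings:

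| Reading of the condition | Consequence |
| --- | --- |
| The data or output address the objectives, whatever they show | The objectives are neutral, so any result of the planned analyses passes, and the condition does no work |
| The data are complete and coherent enough to answer the objectives | A sensible check, but it belongs before the analysis, and no criterion is given |
| The result agrees with what the investigators hope or expect | Reporting depends on the result |

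The text does not choose between these. The first makes the sentence redundant, the second puts it in the wrong place, and the third makes it harmful. None justifies keeping it as written.

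**3. When is it applied?** In the order written, the steps are analysis, PI check, transfer to the statistician, condition, drafting. Both the PI's verification and the condition therefore follow the analysis. The order is also awkward in itself, because an analysis is mentioned before the statistician has the data.

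**4. Who applies it, and with what knowledge?** No judge is named. The only people mentioned in the sentence are the PI and the team who draft the result. The PI performs allocation, discusses laboratory results regularly, and checks the data, in a trial without blinding.

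**5. What happens if the condition is not met?** Nothing is said.

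**6. Is a direction stated anywhere?** Not in the objectives or in the aim within the analysis plan. The Part-A conclusion does state an expected favourable finding.

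**The case against.** The strongest reply is that this is loose English, not a reporting policy. The nearest antecedent of the pronoun in the conditional sentence is the data just sent to the statistician. The objectives are to determine efficacy, so a null result is as consistent with them as a positive one. This stands, and it limits the point. A reader might infer that results will be drafted only if they favour povidone iodine. The Protocol does not say so: it contains no statement that null or unfavourable results will be withheld, and the word 'only' does not appear.

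A reader might also infer that the PI could change RT-PCR calls. The text speaks of discussing laboratory results and of checking and verifying data. It describes no correction, repeat assay or adjudication by the PI, so that inference is not supported.

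The PI's knowledge of arms can be questioned too. The randomization section has the PI hand over opaque sealed envelopes, which a supervisor opens with the nursing supervisor present. But the section on data collection says that the PI performs the allocation, and nothing keeps arm from the PI afterwards.

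Finally, the Protocol promises a data management plan agreed with a Data Monitoring Committee, date- and time-stamped entry, and study numbers on all data and samples. Database-lock mechanics may properly sit in that plan, and their absence here is not a fault. These safeguards do not remove the conditional sentence, which is in the Protocol itself.

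**Conclusion.** The point holds in a limited form. Drafting of the final result depends on an undefined criterion, placed after the analysis, with no path if it is not met. The trial is unblinded, and the PI performs allocation, regularly discusses laboratory results and checks the data before the statistician receives them. This permits result-dependent reporting; it does not show that such reporting is intended.

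The size cannot be quantified from the Protocol. Any figure for the share of misleading reports would need a named primary comparison, a control clearance rate and a directional reading of the condition, and the document supplies none of them. The conclusion assumes that the steps in the analysis plan are meant in the order written. If they are not, the timing criticism weakens, but the undefined condition remains.

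It should be corrected. It does not touch treatment, visits or sample size.

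**What to change.** 1. Delete the conditional sentence, or restate it as a data-completeness check with a stated criterion, made before the analysis.
2. Add: *Results of all prespecified analyses will be reported whatever their direction.*
3. State that RT-PCR samples go to the laboratory under study number only, with arm withheld from laboratory staff and left out of discussions between the PI and laboratory managers.
4. Move the PI's data verification before the analysis.

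Items 1, 2 and 4 are changes of wording and order. Item 3 builds on the study-number labelling already planned, and its small cost is that arm must be kept off laboratory forms and result listings. Because the PI performs allocation, item 3 limits what the PI can link to arm but does not fully mask the PI. Full masking would need a different checker or a protected allocation key, and this point does not depend on that.
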